## **Tertiary Outcomes**

***Surgical Intervention:*** The two groups will be compared with respect to the incidence of the composite endpoint of perioperative and 1-year non-fatal MI (using old definition, see below), all-cause mortality, repeat revascularization (redo CABG or PCI) (major adverse cardiac events, MACE) and stroke.

***Pharmacological Intervention:*** The two groups will be compared with respect to the incidence of the composite endpoint of perioperative and 1-year non-fatal and fatal MI (using old definition, see

below), death, repeat revascularization (redo CABG or PCI) (major adverse cardiac events, MACE) and stroke.

### **Definitions of Study Outcomes**

**Cardiovascular (CV) death:** All deaths in the first 30 days are considered to be CV deaths. All deaths after the first 30 days are considered CV deaths unless a specific non-cardiovascular cause is evident and considered to be the cause of death (e.g. malignancy). Furthermore, patients who die during the index hospitalization but after the initial 30 days period (i.e. long ICU stay with sepsis) will be considered as CV deaths.

**Myocardial infarction:** The pathophysiology of myocardial injury sustained perioperatively is likely different from that when injury is sustained later. Early injury can be a manifestation of either graft occlusion, or of a more general insult secondary to ischemia reperfusion, inflammation, and coronary embolization or spasm. Late injury is likely much more similar to the traditional acute coronary syndrome/atherosclerotic process with native vessel or graft occlusion. The definitions for these events differ as below:

#### **(a) Early perioperative myocardial infarction (within 72 hours of surgery):**

##### **i. New Definition:**

- 1) A CK-MB measurement  $\geq 5$  times the upper limit of normal with new pathological Q waves or new LBBB (Q wave MI) **or** without new pathological Q waves or new LBBB (non-Q wave MI); or
- 2) Angiographic evidence of graft occlusion or native coronary artery occlusion; or
- 3) Imaging evidence of new loss of viable myocardium.

##### **ii. Old Definition:** Early MI is defined as CK-MB $\geq 70$ ng/mL and ECG changes consistent with myocardial injury or CK-MB $\geq 100$ ng/mL in all patients.

**(b) Late perioperative myocardial infarction (later than 72 hours after surgery):** ECG changes consistent with myocardial infarction (new significant Q waves in two contiguous leads) or evolving ST-segment or T-wave changes in two contiguous leads signifying ischemia or new left bundle branch block or ST segment elevation and elevated cardiac markers (troponins or CK-MB) in the necrosis range. Myocardial injury occurring after a PCI are included in the late perioperative Myocardial Injury group but are defined as elevation of cardiac markers  $\geq 3$  times upper limit of normal within 24 hours of PCI or characteristic evolution of new ECG changes.

**New atrial fibrillation:** New onset atrial fibrillation requiring institution of pharmacologic therapy or cardioversion.

**Transfusion requirements:** Autologous blood, homologous processed RBC, whole blood, plasma, platelets, cryoprecipitate will be tracked.

**12 hour chest tube output:** Total chest tube output in the first 12 hours or until the tubes are removed, whichever comes earlier.

**Duration of mechanical ventilation:** Time from ICU admission to first extubation in hours.

**Length of ICU stay and hospital stay:** Time from post-operative ICU admission to ICU discharge (hours) and hospital discharge (days).

**Stroke:** Diagnosis of stroke will require focal neurological symptoms with rapid onset, lasting at least 24 hours. It is strongly recommended (but not required) that an imaging procedure such as a CT scan or MRI be performed. All strokes will be classified as definite ischemic, definite hemorrhagic or type uncertain. A vascular imaging procedure such as a carotid ultrasound is recommended whenever possible (but not required) for subclassification of ischemic strokes into cardioembolic, lacunar or large artery.

**Wound complications:**

Deep mediastinal wound infection: Surgical site infection requiring surgery

Superficial wound infection: Surgical site infection not requiring surgery

Sterile wound dehiscence: Culture negative dehiscence of a wound

**Major Bleed:** Major bleeding that is defined as bleeding greater than 48 hours post-operative and associated with any of the following: death, drop in hemoglobin of at least 2 g/dL, significant hypotension with the need for inotropic agents, bleeding requiring surgical intervention [other than vascular site repair], intracranial hemorrhage, intraocular hemorrhage (excluding subconjunctival hemorrhage), or the requirement for a transfusion of at least 2 U of blood.

**Renal failure:** Requirement for renal replacement therapy (e.g., dialysis, continuous hemofiltration, renal transplant). Hemofiltration or dialysis only during cardio-pulmonary bypass does not constitute a requirement for renal replacement therapy. Patients who receive dialysis within 1 month prior to the surgery are not eligible for this endpoint.

**Repeated coronary revascularization:** New CABG procedure or PCI associated with documented ischemia by ECG *and* graft failure or new culprit lesion ( $\geq 70\%$  luminal stenosis).

**Recurrence of angina:** New onset of typical chest angina with documented ischemia by stress testing (ECG, echocardiography, or nuclear) or persistence of CCS grade  $\geq 2$  angina after the surgery.

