## **2 STUDY OBJECTIVES**

The objective of the pilot phase of the study is to determine the number of eligible patients of the total isolated CABG patients, the consent rate, adherence to the protocol including rate of follow-up cardiac CT angiography, medication discontinuation and the overall incidence of the primary outcome. Achieving a recruitment rate of 1-2 patients/centre/month will determine if the study will proceed to the full phase III trial.

The primary objective of this study for the **Surgical Arm** is to determine whether a novel atraumatic (“no touch”) technique of pedicled saphenous vein graft (SVG) harvesting results in a lower **proportion of study SVGs** that are totally (100%) occluded on 1-year post-CABG angiography and death due to cardiovascular or unknown causes, compared to conventional SVG harvesting techniques, in patients undergoing CABG.

The primary objective of this study for the **Pharmacological Arm** is to determine whether N-3 polyunsaturated fatty acid (fish oil) oral supplementation results in a lower **proportion of patients** with  $\geq 1$  graft (study SVG, non-study SVG or arterial graft) totally (100%) occluded at 1-year post-CABG angiography and death due to cardiovascular or unknown causes, compared to those who received placebo.

The secondary objectives for the **Surgical Arm** are to determine whether:

- i. The “no touch” technique of SVG harvesting results in a lower ***proportion of study SVGs*** that have a significant stenosis (50-99%) on 1-year post-CABG angiography compared to conventional SVG harvesting techniques.
- ii. The incidence and severity of adverse SVG harvesting events at 1-year post-CABG (infection, haematoma, swelling, neuropathy, quality of life measures) are similar between the “no touch” and conventional groups of patients.
- iii. The incidence of the composite of non-fatal myocardial infarction (MI) (using new definition, see Section 5.5), all-cause mortality, and repeat revascularization (redo CABG or percutaneous coronary intervention [PCI]) perioperatively and at 1 year is lower in the “no touch” versus conventional group of patients.

The secondary objectives for the **Pharmacological Arm** are to determine whether:

- iii. Fish oil supplementation results in a lower ***proportion of patients*** with  $\geq 1$  graft with a significant (50-99%) stenosis at 1-year post-CABG angiography, compared to those who received placebo.

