**CONFIDENTIAL**  
SUPERIOR SVG – 2011-06-13

commenced at this visit. Study supplements will not be administered on the day of surgery. Blood will be drawn at induction for the preoperative CK-MB (5 mL draw for preoperative CK-MB). The discharge visit will consist of a patient evaluation and blood work (5 mL draw for 24 hour post-operative CK-MB). At this time, a 3-month supply of the fish oil supplement or placebo will be given (by the Site Study Nurse). The 30-day visit will consist of a patient evaluation, assessment of leg wound, and a drug compliance check. The 3-month visit will consist of a patient evaluation, assessment of leg wound, and drug compliance check. The 6-month and 9-month visits will consist of a patient evaluation and drug compliance check. At the 3-month, 6-month and 9-months visits, a 3-month supply of the fish oil supplement or placebo will be given. The 1-year visit will consist of a patient evaluation, blood work (5 mL draw for serum creatinine), assessment of leg wound, drug compliance check, and cardiac CT angiography (acceptable window for angiography is 9-15 months postoperatively). ECG and blood work (creatinine) information will also be collected at this time as the patient will need to have these tests done prior to undergoing the CCTA. Patients with an estimated GFR < 30 mL/min will not be eligible for the study CT angiography. Patients with an estimated GFR of 30-60 mL/min may undergo the study CT angiography with renal precautions according to the institutional protocol, which may include any or all of the following: saline hydration, sodium bicarbonate loading, n-acetyl cysteine prophylaxis, and temporary stoppage of potentially nephrotoxic drugs and metformin.

**Table 1:** Schedule of follow-up

| VISIT SCHEDULE                  | Pre-op  | OR Day | Discharge | 30 Day | 3 Mth | 6 Mth | 9 Mth | 1 Year |
|----------------------------------------|----------------|---------------|------------------|---------------|--------------|--------------|--------------|---------------|
| Evaluation of Inclusion Criteria       | ✓              |               |                  |               |              |              |              |               |
| Informed Consent                       | ✓              |               |                  |               |              |              |              |               |

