## **Secondary Outcomes**

***Surgical Intervention:*** The two groups will be compared with respect to:

- i. The number of study SVGs with a significant (50-99%) stenosis on 1-year CTA.
- ii. The number of study SVGs with a significant stenosis or total occlusion at 1-year CTA.
- iii. The incidence of and severity of adverse SV harvesting events by 1-year (infection, haematoma, swelling, neuropathy).
- iv. The incidence of the composite endpoint of perioperative and 1-year non-fatal MI (using new definition, see “Early perioperative myocardial infarction (within 72 hours of surgery)” below), all-cause mortality, repeat revascularization (redo CABG or PCI) (major adverse cardiac events, MACE) and stroke.

***Pharmacological Intervention:*** The two groups will be compared with respect to:

- i. The proportion of patients with  $\geq 1$  graft with a significant (50-99%) stenosis on 1-year CTA.
- ii. The proportion of patients with  $\geq 1$  graft with a significant stenosis or total occlusion at 1-year CTA.
- iii. The proportion of venous and arterial grafts considered separately with total occlusion and/or stenosis, defined above.
- iv. The incidence of the composite endpoint of perioperative and 1-year non-fatal MI (using new definition (see “Early perioperative myocardial infarction (within 72 hours of surgery)” below), death, repeat revascularization (redo CABG or PCI) (major adverse cardiac events, MACE) and stroke.

NB: Graft occlusion determines the primary endpoint and graft stenosis, the secondary endpoint, as graft occlusion is generally of greater clinical importance than stenosis. Graft occlusion is the primary mode of SVG failure 1 year postoperatively (7).

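### Repeat revascularization counts only with ischemia documented by ECG, so redo procedures supported solely by stress echo or nuclear imaging drop out of MACE

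*Protocol*

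**What the plan says.** The operative rule is the entry for repeated coronary revascularization in Protocol Section 5.5, under Definitions of Study Outcomes. It requires a "New CABG procedure or PCI associated with documented ischemia by ECG", then an italicised *and*, then either graft failure or a new culprit lesion with at least 70% luminal stenosis. The sentence has no brackets to show how the *and* and the *or* group.

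The next entry, recurrence of angina, accepts new typical angina "with documented ischemia by stress testing (ECG, echocardiography, or nuclear" methods), or persistent angina of CCS grade 2 or more.

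The outcome lists name the component only briefly. In the Secondary Outcomes of Section 5.5, the surgical list has "all-cause mortality, repeat revascularization (redo CABG or PCI) (major adverse cardiac events, MACE) and stroke" and the pharmacological list has "death, repeat revascularization (redo CABG or PCI) (major adverse cardiac events, MACE) and stroke". The Tertiary Outcomes use the same label. Section 2 has "all-cause mortality, and repeat revascularization (redo CABG or percutaneous coronary intervention [PCI]) perioperatively and at 1 year". Section 2 points to Section 5.5 for the MI definition, but no list points to the revascularization entry.

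Section 8.4 names an excess of MACE as a ground on which the DSMB would recommend stopping. Section 8.5 expects MACE of about 10-12% and says that only very large differences could be detected.

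**The concern.** Followed exactly, the rule turns on the test used to show ischemia rather than on whether ischemia was shown. Take a patient with an occluded vein graft, a positive nuclear stress study and a PCI to restore flow. That is a repeat revascularization for graft failure with objective ischemia, yet it is a non-event unless an ECG also showed ischemia. A patient whose ECG is uninterpretable for ischemia, for example because of a paced rhythm, could not meet the rule whatever other tests show.

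These are the clinical consequences of graft failure that both factorial questions aim to reduce. The composite is a secondary outcome of both questions, a tertiary outcome with the older MI definition, and part of what the DSMB watches. Because the rule is the same in all four groups, the main cost is lost events and precision, not a built-in bias. The missing brackets add a separate risk: two careful readers could classify the same procedure differently.

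**Working it through.** The protocol has no figure of its own to reproduce on this point, so the check is logical.

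**Inputs**, all from the revascularization entry in Section 5.5. For a patient who has had a redo CABG or PCI, let E = ischemia documented by ECG, G = graft failure, L = new culprit lesion of at least 70%.

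- Natural reading (the italicised *and* adds a condition): E and (G or L).
- Second reading: (E and G) or L.

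| Case | Natural reading | Second reading |
|---|---|---|
| E, with G or L or both | event | event |
| E, neither G nor L | no event | no event |
| No E; G only | no event | no event |
| No E; L, with or without G | no event | event |
| No E; neither G nor L | no event | no event |

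Two things follow.

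1. The third row is the core of the point. A procedure for a failed graft, with ischemia shown only by stress echo or nuclear imaging, is a non-event under both groupings, unless the failed graft is itself classed as a new culprit lesion. This does not depend on resolving the grammar.
2. The readings disagree only in the fourth row. There the natural reading drops a new lesion even if stress imaging showed ischemia. The second reading counts it even if no test did.

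**Comparison with the angina entry.** Recurrence of angina accepts stress testing by ECG, echocardiography or nuclear imaging. The protocol therefore already treats all three as adequate proof of ischemia.

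**Effect on the MACE rate.** Let p be the MACE rate if all three stress tests were accepted, r the proportion of patients whose only MACE event is a repeat procedure with objective ischemia and G or L, and f the share of those whose ischemia is not documented by ECG. Under the natural reading the rate is p − r × f. The protocol gives 10-12% for MACE overall, does not split it by component, and states neither r nor f. Only the direction is known: under the natural reading, the ECG condition can lower the rate or leave it unchanged.

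**Effect on the sample size.** None. Section 8.5 uses occlusion rates only. The standard two-proportion formula (two-sided 0.05, 80% power, no continuity correction) returns the stated 615 per group for 20% vs 14% and 540 for 30% vs 22.5%. Allowing for 80% angiographic follow-up, 615 / 0.80 = 769 per group, and 2 × 769 = 1,538, against the planned 1,550. Revascularization does not enter.

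**The case against.** The best defence is that an ECG condition is a legitimate endpoint choice. It is specific, it is simple across about 50 centres, and it does not exclude a stress ECG, since the entry does not say resting ECG. Recurrence of angina is a separate outcome outside the MACE composite, so its wider test list cannot change a MACE count. Some excluded procedures would still enter MACE through MI: the late MI definition takes in marker rises of at least three times the upper limit after PCI, and the new early definition takes in angiographic graft occlusion within 72 hours. The italicised *and* also makes the natural grouping fairly clear.

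All of this stands, and it limits the point. It does not explain why stress echo and nuclear imaging are refused here and accepted in the next entry, and it does not help the patient whose ECG cannot show ischemia.

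A reader might infer more than the text supports, in three ways.

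- **That the outcome lists contradict the definition by counting every redo procedure.** They do not. The words in parentheses name the procedure types, and the definitions section then says when one counts. Stroke is handled the same way.
- **That the study CT feeds the clinical endpoint, because scans at 9-12 months could prompt counted procedures and later ones could not.** Section 5.2 does say that the "acceptable window for angiography is 9-15 months postoperatively". But the argument needs the less natural grouping, an assumed spread of scans and a strict month-12 cut-off for MACE, and the protocol states neither of the last two.
- **That a definite number of patients is affected.** No passage gives a revascularization rate or the share without ECG ischemia.

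**Conclusion.** The point holds as a defect in one endpoint definition. On its natural reading, the entry excludes from MACE a redo CABG or PCI for a failed graft or a new lesion of at least 70% when ischemia was shown only by stress echo or nuclear imaging. For a failed graft with no new culprit lesion, the exclusion applies on either reading. The missing brackets are a lesser drafting fault.

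The reach is limited to the secondary and tertiary composites of both factorial questions and to the DSMB's review of MACE, assuming that Section 8.4 uses the term as Section 5.5 does. The size cannot be computed from the protocol, and overlap with MI and death would reduce it. Both primary outcomes and the 1,550 sample size are untouched. This is a worthwhile and nearly free improvement, not a threat to the trial's main conclusions.

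**What to change.** Rewrite the entry so that the grouping is explicit and the accepted tests are listed: redo CABG or PCI, with objective ischemia shown by ECG or by stress testing (ECG, echocardiographic or nuclear), AND (graft failure or a new culprit lesion of at least 70%). Keep the brackets in the protocol text. Cite this definition wherever the composite is listed: the synopsis, Section 2, and the Secondary and Tertiary Outcomes of Section 5.5.

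Measured against the natural reading, the change can only add events, each still requiring objective ischemia and an anatomical cause. It also closes the second reading, under which a lesion alone would suffice.

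The cost is wording, plus slightly more source documentation (the stress-imaging report) for adjudication. Treatment, visits and sample size do not change.

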## **6 SUPPLEMENT SUPPLIES**

### **6.1 Study Supplements**

Patients will receive either fish oil supplements or placebo to be taken twice daily for 1 year post-CABG. Patients will start taking the supplements as soon as they consent and are randomized until their surgery (study supplements not to be administered on day of surgery), and will commence again postoperatively as soon as they are able to take oral medications. The fish oil supplement (Omega Pure 40/20 EE 1000 mg capsules – containing 340 mg eicosapentaenoic acid (EHA) and 170 mg docosahexaenoic acid (DHA)) and placebo (50/50 corn/soybean placebo 1000 mg capsules) will be obtained from Ocean Nutrition Canada. Fish oils or placebo will be given to the patient by the Study Nurse. Patients will receive a bottle containing 185 pills (enough for 3 months) when they are discharged, another bottle at the 3, 6 and 9 month follow-up visits.

### **6.2 Packaging and labeling**

The fish oil supplement and placebo capsules will be packaged, labeled and shipped to the participating sites by Bay Area Research Logistics in Hamilton. The bottles will be labeled with a treatment ID number so as to maintain blinding.

### **6.3 Storage conditions**

Both fish oil supplements and placebo should be stored at room temperature. There are no specific transportation conditions and no special handling requirements. The fish oil supplements and placebo have a shelf life of 3 years.

### **6.4 Responsibilities**

All supplement supplies that will be used in the study must be maintained securely, under the responsibility of the Investigator, or other personnel allowed to store and dispense the supplements, according to the national regulations.

It is the Investigator's responsibility to ensure that an accurate record of supplements issued and returned is maintained.

Under no circumstances will the investigator supply study supplements to a third party, allow the study supplements to be used other than as directed by this protocol, or destroy or dispose of the supplements in any other manner.

## **7 SUBJECT SAFETY**

### **7.1 Monitoring of adverse events**

An **Adverse Event** (AE) is any untoward medical occurrence in a patient or clinical investigation subject who has received treatment; it does not necessarily have to have a causal relationship with this treatment.

A **Serious Adverse Event** (SAE) is any untoward medical occurrence which:

- Results in death, or
- Is life-threatening, or
- Requires in-patient hospitalization or prolongation of existing hospitalization, or
- Is a congenital anomaly/birth defect

The term “life-threatening” in the definition of “serious” refers to an event in which the patient was at risk of death at the time of the event; it does not refer to any event which hypothetically might have caused death if it was more severe. Medical and scientific judgment should be exercised in deciding whether other important medical events should be considered serious. Expected disease-related events/outcomes, other study outcomes or study procedural-related events will not be reported as SAEs but will be reported on specific outcome CRFs. Adverse events will be followed until either resolution or baseline status is achieved.

